**1.0 Background and Rationale**

Preterm birth (PTB) remains the leading cause of neonatal mortality worldwide. Cervical insufficiency is a significant aetiology, and transvaginal cervical cerclage is the standard surgical treatment. Despite widespread use, a substantial proportion of women, particularly those requiring emergency cerclage for cervical dilatation, still deliver preterm. The two-stitch cerclage technique has been proposed as a strategy to provide enhanced mechanical support and potentially restore the cervical mucus plug barrier, thereby reducing the risk of ascending infection and PTB. However, current evidence is derived from limited, heterogeneous retrospective studies with conflicting conclusions. No prior randomised controlled trials have stratified participants by surgical indication to evaluate the efficacy of this technique. This trial aims to provide high-quality evidence on whether a two-stitch cerclage is superior to a traditional one-stitch technique in prolonging pregnancy and improving neonatal outcomes, specifically within therapeutic and emergency cerclage cohorts.

**2.0 Objectives**
2.1 **Primary Objective:** To compare the incidence of spontaneous preterm birth at <34 weeks of gestation between women receiving two-stitch versus one-stitch McDonald cerclage, stratified by indication (therapeutic vs. emergency).
2.2 **Secondary Objectives:** To compare between groups:
Gestational age at delivery.
Spontaneous preterm birth at <28 weeks, <32 weeks and <37 weeks.
Gestational latency (interval from cerclage to delivery).
Postoperative cervical length.
Incidence of preterm premature rupture of membranes (PPROM), chorioamnionitis, and positive cervical culture.
Neonatal survival and morbidity (e.g., NICU admission, RDS, IVH, NEC, sepsis).
Maternal complications.

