**4.0 Participants, Inclusion and Exclusion Criteria**
4.1 **Inclusion Criteria (must meet one category):**
**Therapeutic Cerclage Cohort:** Singleton pregnancy at 16-28 weeks gestation with:
(a) History of spontaneous PTB <34 weeks AND current cervical length (CL) ≤25 mm at 16-28 weeks; OR
(b) No prior PTB BUT documented progressive cervical shortening with CL ≤25 mm at 16-28 weeks
**Emergency Cerclage Cohort:** Singleton pregnancy at 16-28 weeks gestation with painless cervical dilatation, with or without membrane prolapse.
4.2 **Exclusion Criteria:**
(a) Transabdominal cerclage;

(b) Using a pessary for cervical shortening;

(c) Fetal anomalies;

(d) Medically indicated preterm delivery;

(e) Lost to follow-up or incomplete documentation of delivery outcomes.

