**5.0 Interventions**
5.1 **Preoperative preparation:** The basic condition of the patient was fully assessed before surgery, and preoperative examinations were completed to exclude surgical contraindications. The patient was informed of the condition and the risks related to the surgery, and a surgical informed consent form was signed.

5.2 **Surgical procedure:** All patients underwent the McDonald cervical cerclage procedure performed by the same experienced chief gynecologist and obstetrician, using Johnson & Johnson RS22 suture material. During the surgery, the cervix was fully exposed, and several oval forceps were used simultaneously to pull the cervix outward to retract the cervical os. If the amniotic sac protruded beyond the external cervical os, it was reduced to the level of the internal cervical os. In the one-stitch group, the Johnson & Johnson RS22 suture was used to perform a circular continuous suture and knot at the level of the cervicovaginal junction. In the two-stitch group, the first cerclage suture was performed in the same manner as the one-stitch group, and the second suture was performed again in a circular suture near the external cervical os below the first suture to close the external cervical os.

5.3 **Postoperative management:** Patients were placed in a Trendelenburg position for bed rest after surgery. Perioperative antibiotics were used to prevent infection, and external genital hygiene was maintained. Infection indicators, uterine contractions, vaginal discharge, and subjective symptoms of the patient were closely monitored. The changes in the cervix were dynamically monitored by ultrasound. Appropriate tocolytic agents were used according to gestational age and uterine contraction symptoms. The cervical cerclage was usually removed at 36-37 weeks of gestation. In case of definite signs of infection, preterm premature rupture of membranes (PPROM), inevitable miscarriage or preterm labor unresponsive to tocolytic agents, the cerclage should be urgently removed in the emergency department. The timing of cerclage removal should be grasped to reduce the occurrence of cervical laceration.

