**6.0 Outcomes**
6.1 **Primary Outcome:** Spontaneous preterm birth at <34+0 weeks gestation.
6.2 **Secondary Outcomes:** As listed in section 2.2. Gestational dating was standardized using first-trimester crown-rump length (CRL) measurements (11-13 weeks). When discrepancy >7 days existed between last menstrual period (LMP) and ultrasound dating, CRL-based dating was prioritized.

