**8.2 Blinding**

Due to the procedural nature of the intervention, the operating surgeons could not be blinded to the group assignment. However, the following blinding procedures were implemented:

Participants and Postoperative Nursing Staff: Were blinded to group assignment. This was achieved through standardised postoperative care protocols and by omitting documentation of the number of sutures in the patient's accessible medical records.

Outcome Assessors: Were blinded to the treatment allocation. The primary outcome (spontaneous preterm birth at <34 weeks) was determined based on objective criteria not subject to interpretation based on the surgical technique.

Furthermore, the researcher who managed the randomisation information did not participate in any subsequent trial stages. Although unblinded, surgeons were mandated to follow standardised operative checklists and were excluded from outcome evaluations.

This design ensured that potential confounding from clinical indication type was controlled through stratification, while preserving the properties of random allocation within each prognostic subgroup.

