10.4.2 Secondary Outcomes

Dichotomous outcomes (e.g., PTB at <28, <32, <37 weeks; PPROM; chorioamnionitis; neonatal survival; etc.) will be analyzed similarly to the primary outcome, presenting RR with 95% CI and using Chi-square or Fisher's exact test.

Continuous outcomes:

Normally distributed variables (e.g., gestational age at delivery in the emergency cohort PP analysis) will be presented as mean ± SD and analyzed with Independent Samples t-tests, reporting the mean difference with 95% CI.

Non-normally distributed variables (e.g., gestational latency, GA at delivery in the therapeutic cohort) will be presented as median (Q1, Q3) and analyzed with the Wilcoxon rank-sum test, with the median difference and its 95% CI calculated via the Hodges-Lehmann method.

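### Postoperative cervical length is compared without the preoperative length held for every woman in the therapeutic cohort, from an unnamed scan, under an assessor-blinding statement not supported for this outcome

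*Protocol*

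**What the plan says.** Section 2.2 lists "Postoperative cervical length" among the secondary objectives. Section 6.2 defines the secondary outcomes only by reference back ("As listed in section 2.2") and adds a rule for gestational dating, with nothing on cervical length. The only postoperative cervical imaging described is in section 5.3: "The changes in the cervix were dynamically monitored by ultrasound". No schedule, number of scans or index scan is given.

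Preoperative length is an entry criterion on both routes into the therapeutic cohort in section 4.1; the first route reads "current cervical length (CL) ≤25 mm at 16-28 weeks" and the second has the same limit. Entry to the emergency cohort is by "painless cervical dilatation, with or without membrane prolapse", with no length required.

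Under section 10.4.2, normally distributed continuous outcomes are "analyzed with Independent Samples t-tests, reporting the mean difference with 95% CI". The others get a rank-sum test with a Hodges-Lehmann interval. Neither uses a covariate.

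On blinding, section 8.2 says "Outcome Assessors: Were blinded to the treatment allocation". The supporting sentence that follows concerns the primary outcome only. Section 5.2 describes what differs between the arms: in the two-stitch group, "the second suture was performed again in a circular suture near the external cervical os below the first suture to close the external cervical os".

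**The concern.** Cervical length is the listed outcome closest to the mechanical support that section 1.0 gives as a rationale for the second stitch, so readers will look to it for a mechanism. Three features weaken it.

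- **Precision.** The analysis leaves between-woman variation in starting length in the error term, although in the therapeutic cohort that length is already on file. With 25 women per arm per stratum, precision is scarce.
- **Blinding.** The general statement covers an outcome read from an image of the organ that carries the intervention, with the second suture placed close to one end of the length being measured. No masked reading is described.
- **Index value.** If a woman has more than one postoperative scan, nothing says which value counts. A late scan also exists only for women who are still pregnant.

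**Working it through.** **The plan's own figure.** The protocol gives no precision or power figure for cervical length. Its stated 44 women for the emergency stratum (section 7.0) concerns the primary outcome. It reproduces closely: at 89.5% versus 42.1%, Fisher's exact test with 22 per arm has 89.8% power, and the continuity-corrected formula gives 23 per arm, 46 in total. The only input taken from section 7.0 for the precision step is 25 per arm per stratum.

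**Precision: inputs.** n = 25 per arm (section 7.0). The pre/post correlation r is not in the document, so 0.3, 0.5 and 0.7 are assumed. Results are in units of the standard deviation (SD) of postoperative length.

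**Precision: formulas.**
- Unadjusted 95% CI half-width = t(0.975, 48) × √(2/25) = 2.011 × 0.283 = 0.57 SD.
- ANCOVA multiplies the standard error by √(1 − r²) and uses 47 degrees of freedom.
- Equivalent unadjusted sample size = 25 / (1 − r²) per arm.

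| r | 1 − r² | √(1 − r²) | CI narrower by | Half-width (SD) | Detectable at 80% power (SD) | Equivalent n per arm |
|---|---|---|---|---|---|---|
| unadjusted | 1 | 1 | – | 0.57 | 0.81 | 25 |
| 0.3 | 0.91 | 0.954 | about 5% | 0.54 | 0.77 | 27.5 |
| 0.5 | 0.75 | 0.866 | about 13% | 0.49 | 0.70 | 33.3 |
| 0.7 | 0.51 | 0.714 | about 29% | 0.41 | 0.58 | 49.0 |

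The 25 mm entry limit narrows the range of preoperative lengths, which may pull r towards the lower rows.

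**Blinding.** No arithmetic applies. Section 8.2 makes a claim about all outcome assessors, and the reason it gives (objective criteria that do not depend on surgical technique) is stated for birth before 34 weeks. Section 5.2 puts one circular suture on the cervix in one arm and two in the other. Section 5.3 has that cervix followed by ultrasound. Nothing says who reads the length or how that reader is kept from knowing the arm. The stated reason therefore does not reach this outcome.

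**Index scan.** Suppose the analyst could choose freely among k scans, with an assumed between-scan correlation of 0.9 down to 0.3, 25 women per arm and no true effect. By simulation, the chance that at least one t-test reaches p < 0.05 is about 7.5% to 10% for k = 2, 8% to 14% for k = 3 and 10% to 21% for k = 5. One pre-specified scan keeps it at 5%.

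**Availability at late scans.** The planning rates imply 25 × 0.895 = 22.4 versus 25 × 0.421 = 10.5 emergency deliveries before 34 weeks. This describes depletion only for a scan near 34 weeks. In that extreme case, with an assumed correlation of 0.3 to 0.5 between length and latency, restricting to women still pregnant raises the one-stitch mean relative to the two-stitch mean by about 0.3 to 0.5 SD with no true effect on length. For a scan soon after surgery the document gives no delivery rate, so the depletion cannot be computed.

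**The case against.** The strongest reply is that an unadjusted comparison after 1:1 randomisation within strata is valid. Adjustment is then a matter of efficiency, its benefit rests on a correlation the document does not give, and covariates are often left to a separate analysis plan. Most of this stands: there is no bias here, and the gain could be as small as 5%. The last part does not fully answer the point, because section 10.4.2 already fixes the test and the covariate is already collected in the therapeutic cohort. In the emergency cohort preoperative length is not an entry measurement, so the adjustment point is not firm there.

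A second reply is that the outcome may simply mean one early postoperative scan. That is possible. A reader might infer that a scan has been picked to suit the result, or that the emergency comparison is between arms already depleted by 22 of 25 and 11 of 25 deliveries. The document supports neither. It does not say how many scans each woman has, does not tie them to the outcome, and gives no hint that the index scan is near 34 weeks. What stands is that the outcome is open to selection, and to differential availability if a late scan is used.

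A third reply is that nothing says the sonographer can see or count the sutures, or is the person who records the length. That also stands. It rules out saying that the blinding statement is false or that the measurement is unblinded; it does not supply the missing support.

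**Conclusion.** The point holds as a matter of precision and accurate description, not of bias. In the therapeutic cohort, leaving out preoperative length costs about 5%, 13% or 29% of confidence-interval width at assumed correlations of 0.3, 0.5 or 0.7, possibly nearer the low end because of the 25 mm cap. The assessor-blinding statement is unsupported for cervical length, though not shown to be wrong. The unnamed index scan is mainly a missing detail. Its error-rate figures (7.5% to 21%) apply only if there are several scans and the choice is made freely, and the late-scan shift only if a scan near 34 weeks is used. This is one of many secondary outcomes, and the primary conclusion does not depend on it.

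**What to change.** - **Section 10.4.2:** estimate the therapeutic-cohort difference in postoperative cervical length by ANCOVA with preoperative length as covariate, reporting the adjusted mean difference and 95% CI. In the emergency cohort, adjust only if a preoperative measure is recorded for all women; otherwise keep the unadjusted comparison.
- **Section 2.2 or 6.2:** take the first routine postoperative scan as the single index value and report later scans descriptively. Report by arm how many women had no such scan, since the impute-as-event rule in section 10.2 has no meaning for a length.
- **Section 8.2:** limit the blinding claim to the outcomes it covers, or describe masked reading of cervical length if it is done.

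The cost is wording and one degree of freedom. No new measurement is needed, provided the routine monitoring in section 5.3 gives each woman at least one postoperative scan. The small downside is a less favourable blinding statement if masked reading was not done.

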**3.0 Trial Design**
A single-centre, stratified, parallel-group, randomised, controlled, superiority trial. The study will be conducted at Fujian Maternity and Child Health Hospital, Fuzhou, China.

**4.0 Participants, Inclusion and Exclusion Criteria**
4.1 **Inclusion Criteria (must meet one category):**
**Therapeutic Cerclage Cohort:** Singleton pregnancy at 16-28 weeks gestation with:
(a) History of spontaneous PTB <34 weeks AND current cervical length (CL) ≤25 mm at 16-28 weeks; OR
(b) No prior PTB BUT documented progressive cervical shortening with CL ≤25 mm at 16-28 weeks
**Emergency Cerclage Cohort:** Singleton pregnancy at 16-28 weeks gestation with painless cervical dilatation, with or without membrane prolapse.
4.2 **Exclusion Criteria:**
(a) Transabdominal cerclage;

(b) Using a pessary for cervical shortening;

(c) Fetal anomalies;

(d) Medically indicated preterm delivery;

(e) Lost to follow-up or incomplete documentation of delivery outcomes.

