**8.0 Randomisation and Blinding**
**8.1 Randomisation**

Participants were primarily stratified by clinical indication (Therapeutic cerclage cohort vs. Emergency cerclage cohort, n=50 per stratum). Within each stratum, they were randomly assigned (1:1) to receive either the one-stitch or two-stitch technique (n=25 per group) using a computer-generated random number sequence (created with SPSS 26.0) with permuted blocks of sizes 4 and 6.

Allocation concealment was implemented using sequentially numbered, opaque, sealed envelopes. For each eligible participant, an independent research nurse provided the corresponding envelope directly in the operating room. The envelope was opened by the surgeon only after anaesthesia preparation and the final decision to proceed with surgery. The surgeon had no access to the master allocation sequence, and only one envelope was present in the operating room at any time. Stratum-specific randomisation lists were maintained independently to prevent cross-stratum contamination.

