**10.0 Statistical Analysis Plan**

**10.1 Analysis Principles**

The primary analysis will be performed according to the intention-to-treat (ITT) principle, including all randomly assigned participants in the groups to which they were originally allocated.

A supporting per-protocol (PP) analysis will also be conducted, which excludes participants who did not receive the allocated intervention or who had major protocol violations.

A two-sided p-value of less than 0.05 will be considered statistically significant for the primary outcome. All analyses will be performed using SPSS software (version 26.0, IBM SPSS, Inc, Armonk, NY).

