**10.2 Handling of Missing Data**

For the primary and secondary outcome, if data are missing, a conservative approach will be applied by imputing the missing participants as having experienced the event in the primary ITT analysis.

The PP analysis will simply exclude participants with missing primary outcome data.

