**10.5 Time-to-Event Analysis**

Time-to-event data (gestational age at delivery) were analyzed using Kaplan-Meier survival curves and compared with the log-rank test. Participants who did not experience the primary event (spontaneous preterm birth <34 weeks) were administratively censored. Specifically, censoring occurred at the gestational age of term delivery, medically indicated (iatrogenic) delivery, study withdrawal (e.g., due to protocol violations or subsequent ineligibility), or loss to follow-up (last known gestational age with confirmed pregnancy status).

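### Exclusion criteria 4.2(d) and 4.2(e) can only be known after randomisation, and applying them contradicts the ITT set and the missing-data rule

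*Protocol*

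**What the plan says.** Section 4.2 of the Protocol lists five exclusion criteria. Two of them describe the end of the pregnancy or the record of it: (d) "Medically indicated preterm delivery" and (e) "Lost to follow-up or incomplete documentation of delivery outcomes".

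Entry is at 16-28 weeks in both cohorts; the emergency criterion, for example, reads "Singleton pregnancy at 16-28 weeks gestation with painless cervical dilatation, with or without membrane prolapse". Section 8.1 fixes the moment of allocation: "The envelope was opened by the surgeon only after anaesthesia preparation and the final decision to proceed with surgery".

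The analysis sections treat the same women differently:

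- Section 10.1 defines the primary analysis as ITT, "including all randomly assigned participants in the groups to which they were originally allocated".
- Section 10.2 handles missing outcomes by "imputing the missing participants as having experienced the event in the primary ITT analysis". It confines exclusion for missingness to the supporting analysis: "The PP analysis will simply exclude participants with missing primary outcome data".
- Section 10.5 keeps women in the time-to-event analysis: "Participants who did not experience the primary event (spontaneous preterm birth <34 weeks) were administratively censored". Its list of censoring reasons includes both medically indicated delivery and loss to follow-up.

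Section 6.1 defines the primary outcome as spontaneous birth before 34+0 weeks. No section says whether 4.2 or the analysis rules prevail.

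**The concern.** An eligibility criterion has to be decidable before allocation. Criterion (d) is a delivery outcome that competes with the primary outcome, and (e) is the missingness of that outcome. Criterion (e) has no pre-randomisation reading, and (d) is not worded as obstetric history. If either is applied, women leave the analysis after allocation for a reason that may differ between arms, and randomisation no longer protects the comparison.

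What is at stake is the primary analysis set. Two analysts following the same document could report different denominators and different relative risks, each with a passage to cite. Criterion (d) also sets no lower gestational limit of its own, so it would delete a woman delivered on medical indication at, say, 35 weeks, whose primary outcome is already known to be a non-event.

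**Working it through.** **1. The passages side by side**

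| Woman | Section 4.2 | Primary binary ITT analysis | Section 10.5 |
|---|---|---|---|
| Lost, or delivery outcome not documented | excluded (e) | kept, counted as event (10.1, 10.2) | kept, censored (the loss case) |
| Medically indicated birth before 34+0 weeks | excluded (d) | kept; non-event, because not spontaneous (6.1, 10.1) | kept, censored |

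The first column conflicts with both others. The second and third do not conflict with each other, since they are two analyses with their own conventions.

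**2. The plan's own figure.** Section 7.0 gives 44 women for the emergency stratum from 89.5% vs 42.1%, 90% power and two-sided alpha 0.05. The normal-approximation formula gives 19 per arm (38) without continuity correction and 23 per arm (46) with it. Exact power of Fisher's test at 22 per arm is 89.8%. The stated 44 therefore reproduces. With 22 to 24 women left per arm, approximate power on these rates is still 94% to 96%, so the problem is not loss of power.

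**3. Size for criterion (e).** The event counts are assumed. The arm size of 25 comes from section 7.0. Suppose 16/25 events in the one-stitch arm, and in the two-stitch arm 3 women lost and 7 events among the other 22.

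Formulas: RR = (a/n1)/(b/n2), two-stitch over one-stitch; Pearson chi-square = N(ad - bc)^2 divided by the product of the four margins. Every expected count is at least 5, so the rule in section 10.3 points to chi-square.

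- Excluded under 4.2(e), 7/22 vs 16/25: RR = 0.318/0.640 = 0.50 (95% CI 0.25 to 0.98). Chi-square = 47 x (7x9 - 15x16)^2 / (22x25x23x24) = 1,472,463/303,600 = 4.85, p = 0.028 (Fisher 0.041).
- Kept under 10.2, 10/25 vs 16/25: RR = 0.400/0.640 = 0.63 (0.36 to 1.10). Chi-square = 50 x (10x9 - 15x16)^2 / (25x25x26x24) = 1,125,000/390,000 = 2.88, p = 0.089 (Fisher 0.156).

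**4. Range for criterion (e).** Other assumed counts move the RR without crossing 0.05:

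- 2 two-stitch women lost: 7/23 vs 14/25 (RR 0.54) if excluded, 9/25 vs 14/25 (RR 0.64) under 10.2.
- 3 two-stitch women lost, 8 events in the rest: 8/22 vs 16/25 (RR 0.57) against 11/25 vs 16/25 (RR 0.69).
- 3 one-stitch women lost instead: 10/25 vs 13/22 (RR 0.400/0.591 = 0.68) if excluded, 10/25 vs 16/25 (RR 0.63) under 10.2. Exclusion now weakens the apparent effect.

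**5. Size for criterion (d).** Assume 11/25 two-stitch vs 22/25 one-stitch events, RR 0.50. Women with indicated delivery are non-events, so removing them shrinks only the denominator.

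| Women removed | Removed from two-stitch: RR | Removed from one-stitch: RR |
|---|---|---|
| 1 | (11/24)/(22/25) = 0.52 | (11/25)/(22/24) = 0.48 |
| 2 | (11/23)/(22/25) = 0.54 | (11/25)/(22/23) = 0.46 |
| 3 | (11/22)/(22/25) = 0.57 | (11/25)/(22/22) = 0.44 |

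The direction depends on the arm in which these deliveries fall, which the documents do not tell.

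**The case against.** The strongest reply is that the analysis sections already do the right thing. Section 10.1 keeps everyone, section 10.2 imputes missing outcomes and limits exclusion for missingness to the per-protocol set, and section 10.5 keeps these women and censors them. On that reading 4.2(d) and (e) are misplaced remnants, and the intention is retention. This stands in part: the document contradicts itself rather than setting out a settled plan to drop women. But nothing ranks the sections, and 10.5 itself mentions withdrawal for later ineligibility, so the contradiction has to be removed.

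The illustration in (e) is also open to challenge. Three losses in one stratum are 3/50 = 6%, slightly above the 5% allowance in section 7.0, and all are placed in one arm. With a continuity correction the excluded table gives p = 0.056. It shows sensitivity and forecasts nothing.

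Three stronger readings are tempting and are not supported:

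- A reader might infer that births after infection or PPROM would be labelled medically indicated, so that (d) removes treatment failures. Section 5.3 covers removal of the suture and says nothing about how the later birth is classified.
- A reader might infer that exclusion under (d) manufactures significance, for example by moving 18/25 vs 13/25 (RR 0.72, p = 0.145) to 18/25 vs 9/21 (RR 0.60, p = 0.046). That mixes relabelling four births with excluding them. If the four are medically indicated they are non-events under 6.1, and the ITT table is 18/25 vs 9/25 (RR 0.50, p = 0.011). Excluding them then moves the result towards the null.
- A reader might call an event or non-event in the binary analysis incompatible with censoring in the Kaplan-Meier analysis. These are different analyses, and section 10.2 does not address the second.

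**Conclusion.** The point holds in this form: 4.2(d) and (e) are post-randomisation conditions placed among the eligibility criteria, and applying them contradicts sections 10.1, 10.2 and 10.5. The contradiction rests on the text alone and needs no assumption.

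Its numerical effect does rest on assumed counts, because the documents give no rate of indicated delivery and, for loss, only the 5% allowance. With 25 women per arm, three exclusions are 12% of an arm. In the assumed cases such exclusions change the RR by up to about 0.13, and in one of them p lies on either side of 0.05 depending on the rule used. The size and direction of any bias in this trial cannot be stated, and no claim that it favours either technique is warranted. The point needs correcting because the primary analysis set is otherwise open to choice after the outcomes are known.

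**What to change.** - Delete (d) and (e) from section 4.2.
- State in 10.1 that every randomised woman is in the primary ITT analysis, and that no criterion assessed after the envelope is opened removes her from it.
- Handle missing primary outcomes in that analysis by section 10.2 only.
- State in 6.1 and 10.4.1 that a medically indicated birth before 34+0 weeks stays in the denominator as a non-event of the spontaneous outcome. The sponsor should also state how births are classified as spontaneous or indicated; the present text does not, and that boundary is the sponsor's to set.
- Add all-cause birth before 34+0 weeks as a supporting ITT analysis, which does not depend on that classification.

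The cost is protocol wording and one extra 2x2 table per stratum. The sample size does not change. If women have already been removed under (d), those with recorded deliveries can be returned to the analysis. Women removed under (e) whose outcome is truly unknown cannot be recovered from delivery records and enter through the 10.2 rule.
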